### Case Definition: Composite Reference Standard

All patients with suspected leprosy referred to the outpatient clinic of the UHB will be included. Included patients will be subject to a standardized clinical evaluation and complementary evaluations. Allocation to the leprosy group will be conducted according to the WHO criteria [32], with allocation to the nonleprosy group being reserved for those patients referred by the primary care physician due to suspected leprosy who do not fulfill the WHO’s criteria [32]. Neither ultrasound nor molecular examinations performed on the perineural aspirate will be used in the allocation process. Collection of clinical data and ultrasound examinations with perineural aspirate will be performed on the same day. The diagnostic evaluation will be performed before the index test; as a result, the diagnostic classification provided by the index text will not be known by those responsible for accessing the composite reference standard. Inclusion will occur only after all standard diagnostic tests are conducted.

### Exclusion Criteria

Patients with the following comorbidities causing neuritis or neuropathy will be excluded: diabetes, hypothyroidism, HIV, trauma-related peripheral neural disease, hereditary neuropathy, autoimmune diseases, and alcoholism. Patients with relapsed leprosy who had ulnar nerve transposition and patients who, at the initial ultrasonographic examination, present anatomical alterations that may increase the risk of or bring additional risks to the subcutaneous aspirate process will also be excluded.

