Clinically, the evaluation of possible nervous involvement is conducted via neurological examination in search of sensorimotor deficit and through palpation of nerves to evaluate nervous thickening [16]. In the appropriate clinical context, the presence of signs of peripheral neuropathy is often diagnostic for leprosy. The time when neurological deficit has already developed constitutes a very late stage for diagnosis, resulting in irreversible sequelae [17]. In addition, peripheral nerve palpation is examiner dependent and has low accuracy in the diagnosis of the disease [18].

Ultrasound has higher spatial resolution when compared with magnetic resonance imaging, which results in higher sensitivity with equivalent specificity to detect focal peripheral nerve pathology [19]. It is a noninvasive and low-cost method that provides real-time and dynamic examination, enabling the acquisition of accurate morphological information (diameter and fascicular abnormalities) without side effects for the patient. Through the Doppler mode, it is also possible to know whether there is an increase in local vascular flow indicating an inflammatory process [20,21]. Additionally, the test is also used for therapeutic procedures and for the collection of biological material in a minimally invasive way [22]. We hypothesize that minimally invasive perineural aspiration by means of high-frequency ultrasonography is feasible and that PCR performed in the aspirate will be accurate to diagnose leprosy. As the neural sequelae related to leprosy greatly impact the quality of life of patients, it is essential to improve diagnosis with a focus on neural involvement. We believe that the association of ultrasonography with minimally invasive techniques for peripheral nerve assessment is an interesting strategy to achieve this goal.

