Conventional diagnostic tests	Slit skin smear results, bacillary index, and histopathological findings from skin or nerve biopsy (when performed)
Index test—PCR^b^ from perineural aspirate	PCR detection of Mycobacterium leprae targets: RLEP, sodA, and 16S rRNA^c^
Complementary diagnostic test—ultrasound examination	Nerves evaluated: median nerve (carpal tunnel and pronator quadratus), ulnar nerve (ulnar tunnel, immediately before the ulnar tunnel, Guyon canal, and immediately before the Guyon canal), common fibular nerve (fibular head), and tibial nerve (tarsal tunnel and 4 cm above the tarsal tunnel); CSA^d^ measurements; asymmetry indexes (change in CSA^e^ and CSA ratio); focality indexes (change in TPT^f^ and TPT ratio); intraneural or epineural Doppler signal (hypervascularity); nerve echogenicity (normal or abnormal); loss of fascicular pattern; and focal nerve thickening
Reference standard (composite clinical diagnosis)	Presence of ≥1 cardinal sign of leprosy: (1) definite sensory loss in a hypopigmented or reddish skin lesion, (2) thickened or enlarged peripheral nerve with sensory loss and/or muscle weakness, and (3) acid-fast bacilli in slit skin smear

^a^WHO: World Health Organization.

^b^PCR: polymerase chain reaction. PCR targets: RLEP, sodA, and 16S ribosomal RNA of *M leprae*.

^c^rRNA: ribosomal RNA.

^d^CSA: cross-sectional area of the nerve.

^e^Absolute difference between contralateral nerves.

^f^TPT: difference between the thickest and thinnest points along the nerve.

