Through our study, we will be able to demonstrate a high sensitivity of the perineural aspirate in patients with paucibacillary forms of the disease. Preliminary studies in patients that have undergone nerve biopsies have shown both a high sensitivity (92% using PCR) [45] and higher bacillary index of nerve sampling compared to skin sampling [46]. The current diagnostic strategy, which samples for the microbiological diagnosis of leprosy from skin lesions, earlobes, and 3 to 6 representative skin locations [47,48], has an especially low sensitivity in paucibacillary, pure neural, and early-stage lesions [49,50], resulting in diagnostic delays, misdiagnosis [51], and mistreatment. Our potentially higher diagnostic sensitivity in paucibacillary forms is a consequence of the traditional pattern of sample collection not matching the pattern of distribution and homing of *M leprae* in the natural history of the disease. The peripheral nervous system seems to be the first to harbor this mycobacterium [52] and is the location of persistent parasites after treatment of multi-bacillary disease [53].

In this study, we will evaluate both RLEP and RNA targets (sodA and 16S). Previous studies have evaluated a variety of PCR targets to detect *M leprae* in tissues, with the most frequently used being RLEP [13]. Despite its high specificity, the use of this target can only detect 75% of patients with leprosy [13], and its positivity is not related to the viability of the microorganism [15]. We expect to obtain high assay sensitivity using these tests in parallel, as it has been proposed in other studies [14]. As *M leprae* viability is an important clinical question in leprosy, especially in terms of differentiating reaction from relapse, we will also use RNA targets. Their use better correlates with active microorganisms as this nucleic acid is less resistant to temperature and has a shorter half-life [54], being already used for viability evaluation in preliminary studies [15,41]. Thus, our proposed test is also expected to deliver information on the viability of *M leprae* in the aspirate.

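### Previously treated patients can enter the accuracy cohort, neither test is defined to separate old from active disease in them, and Table 1 records no treatment history with which to examine it

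*Protocol article*

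**What the plan says.** **Entry.** Case Definition: Composite Reference Standard states: "All patients with suspected leprosy referred to the outpatient clinic of the UHB will be included". Exclusion Criteria mentions relapse once: "Patients with relapsed leprosy who had ulnar nerve transposition". No section limits entry to patients never treated for leprosy.

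**Reference standard.** Table 1 (Clinical Data) requires "Presence of ≥1 cardinal sign of leprosy". One of the three signs is a "thickened or enlarged peripheral nerve with sensory loss and/or muscle weakness". No condition on disease activity or completed treatment is attached.

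**Index test.** PCR Positivity Criteria sets positivity for a DNA or an RNA sample at a Ct of 30 or less. Expected Findings says of RLEP that "its positivity is not related to the viability of the microorganism", and that the peripheral nervous system "is the location of persistent parasites after treatment of multi-bacillary disease". It expects the DNA and RNA targets to be used in parallel, and names telling a reaction from a relapse as a clinical question.

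**Data.** Clinical Data presents Table 1 as the full list of variables. It includes contact with a leprosy case, but not the patient's own earlier leprosy, earlier treatment, or treatment status when the aspirate is taken.

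**The concern.** The main result is the accuracy of PCR on the perineural aspirate in patients with suspected leprosy. In a never-treated suspect, a cardinal sign and bacterial DNA in the nerve both point to current disease. In a previously treated suspect, that link is weaker for both tests. An old nerve lesion can satisfy the nerve sign, and residual DNA can make the aspirate positive.

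Two errors follow. If old nerve damage puts a patient without active disease into the leprosy group, the aspirate result enters sensitivity although there is no active disease to detect. If the patient has no current cardinal sign but carries residual DNA, the result counts as a false positive. The reported sensitivity and specificity would then depend partly on how many such patients the clinic happened to receive, and the listed data would not show how many there were. For these patients the first RNA sample is also not a value from before any treatment, which affects the before/after comparison.

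**Working it through.** **1. Can they enter?** The inclusion sentence covers all referred suspects. The relapse exclusion is restricted to those with ulnar nerve transposition, a restriction that has a purpose only if other relapsed patients are eligible. Entry is an inference from these two sentences, but a close one.

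**2. Does the reference standard separate old from active disease?** One sign suffices, and the nerve sign carries no activity condition. Background says: "The time when neurological deficit has already developed constitutes a very late stage for diagnosis, resulting in irreversible sequelae". That supports lasting deficit. It does not say that thickening lasts, and the nerve sign needs both. So an old lesion *may* meet the standard; the article does not show that it always does.

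**3. Does the index test separate them?** RLEP DNA is stated to be unrelated to viability. The RNA targets address viability, but no rule lets a negative RNA result override a positive DNA result.

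**4. The plan's own figure.** Sample Calculation gives 54 per group from 50% versus 70% sensitivity, P<.05, power above 0.80 and 10% for losses. The test is not named. An exact one-sample binomial test (two-sided 0.05) needs 49 patients with success at 32 or more positive: upper-tail error 0.0222, power 0.810. Then 49 × 1.10 = 53.9, so 54. The figure is reproduced and is used below as a yardstick.

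**5. Specificity.** Let f be the share of the nonleprosy group that was previously treated and q the chance that residual DNA is detected. Ignoring background false positives, the loss is f × q. Both inputs are assumptions; q = 0.5 here.

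| f | loss | extra false positives of 54 |
|---|---|---|
| 0.05 | 2.5 points | 1.35 |
| 0.10 | 5 points | 2.7 |
| 0.20 | 10 points | 5.4 |

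**6. Sensitivity.** Let f now be the share of the leprosy group that was previously treated and has no active disease, and s the sensitivity in the rest. Apparent sensitivity = (1 − f) × s + f × q.

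| s | f | q = 0.3 | q = 0.5 | q = 0.9 | q = 1.0 |
|---|---|---|---|---|---|
| 0.50 | 0.10 | 0.48 | 0.50 | 0.54 | 0.55 |
| 0.50 | 0.20 | 0.46 | 0.50 | 0.58 | 0.60 |
| 0.70 | 0.10 | 0.66 | 0.68 | 0.72 | 0.73 |
| 0.70 | 0.20 | 0.62 | 0.66 | 0.74 | 0.76 |

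The bias is upward when q exceeds s and downward when q is below s. For example, 0.8 × 0.70 + 0.2 × 0.50 = 0.66, which is below 0.70.

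**7. Effect on the test.** Under the 49-patient rule with s = 0.50 and q = 0.9, the chance of wrongly declaring sensitivity above 50% rises from 0.022 to 0.073 (f = 0.10) or 0.187 (f = 0.20). With q = 0.5 it does not change.

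**The case against.** **Relapse is active disease.** A relapsed patient with a cardinal sign and a positive aspirate is a true positive. A reader might infer from the exclusion criterion that relapsed patients as such corrupt the estimate. The article does not support that. The difficulty is confined to previously treated patients with sequelae or a reaction, and no sentence says outright that they are enrolled.

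**The referral path is diagnostic.** Patients come as suspects, and assessments are timed at diagnosis and one year after treatment begins, which fits poorly with patients who only carry old damage. This makes a large share less likely. It does not exclude suspected relapse or reaction.

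**An external professional decides, with a clinical history.** This person may set old disease aside. How the cited WHO criteria treat completed therapy cannot be checked here. So it cannot be said that a cured patient *will* be put in the leprosy group, only that no rule written in the article prevents it.

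**Direction.** A reader might infer that pooling flatters the test because old damage and old DNA occur in the same person. Step 6 shows that this holds only if residual DNA is found more often than the test's sensitivity in active disease. The article gives no rate for residual DNA, and limits its persistence statement to multi-bacillary disease.

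**Spectrum.** Consecutive enrolment of all suspects matches the population in which the clinic would use the test, and barring treated patients would narrow it. This stands, and is why enrolment should not change. Subgroup reporting may also be left to a fuller document. The list of collected variables, however, is given here as complete, and without the field no later document could define the subgroup from the listed data.

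**Conclusion.** The point holds in limited form. As written, previously treated suspects can enter, and in those with sequelae or reaction either test may be positive without active disease. Accuracy then depends on an unrecorded case mix. The size is unknown. Under assumed shares of 5% to 20% and 50% DNA detection, specificity falls by 2.5 to 10 points; under a 20% share, a sensitivity of 70% becomes anything from 62% to 76% as detection runs from 30% to 100%. If very few treated patients are referred, the effect is negligible, but the listed variables would not allow anyone to show that. The missing treatment history is the firmest part of the finding. The article does not support a claim that the test is necessarily favoured, or that these patients must be kept out of the study.

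**What to change.** 1. Add two fields to Table 1 and REDCap: previous leprosy treatment, and current treatment status at the first aspirate. Recruitment is stated to run from January to December 2026, so add them promptly and complete them from clinic records for anyone already enrolled, where the records allow.
2. Keep consecutive enrolment of all suspects.
3. Prespecify sensitivity and specificity in never-treated patients as the main analysis, or at least as a named sensitivity analysis beside the pooled result.
4. Report previously treated patients separately, for accuracy and in the before/after RNA comparison.

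**Cost.** Two history items and one analysis-set sentence, with slightly less precision in the never-treated analysis. At 70% sensitivity the approximate 95% half-width is 1.96 × √(0.21/n): 12.2 points with n = 54, 12.9 with n = 48.6 (10% previously treated) and 13.7 with n = 43.2 (20%). A 10% share would use up roughly the whole loss allowance in that group (54 against 49 evaluable), so a larger share would call for somewhat longer recruitment or acceptance of lower power in that analysis.

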### Clinical Data

The following clinical and complementary variables will be collected: age, sex, place of residence, occupation, history of household or close contact with a leprosy case, duration of symptoms, type of presenting symptoms (eg, sensory loss, paresthesia, pain, or muscle weakness), number and anatomical distribution of skin lesions, morphological characteristics of lesions (hypopigmented, erythematous, infiltrated, or nodular), presence of sensory loss within skin lesions, presence of peripheral nerve thickening on physical examination, nerves affected, sensory impairment on neurological examination, motor impairment, disability grade at diagnosis according to the WHO criteria, clinical classification of leprosy, operational classification according to WHO criteria (paucibacillary or multi-bacillary), and classification according to the Ridley-Jopling spectrum (indeterminate, tuberculoid, borderline tuberculoid, midborderline, borderline lepromatous, and lepromatous). Complementary diagnostic data will include SSS results and bacillary index when available, as well as histopathological findings from skin or nerve biopsy when performed. A standardized simplified neurological examination according to Brazil’s Ministry of Health guidelines will be conducted for all patients [33]. Table 1 aggregates all variables to be collected, and Figure 1 summarizes the study timeline.

**Table 1 table1:** Variables to be collected.

Category	Variables
Participant characteristics	Age, sex, place of residence, occupation, and history of household or close contact with a leprosy case
Clinical and disease characteristics	Duration of symptoms, type of presenting symptoms (sensory loss, paresthesia, pain, and muscle weakness), number of skin lesions, anatomical distribution of skin lesions, morphology of lesions (hypopigmented, erythematous, infiltrated, and nodular), sensory loss within lesions, peripheral nerve thickening on physical examination, nerves affected, sensory impairment on neurological examination, motor impairment, disability grade at diagnosis (WHO^a^ criteria), clinical classification of leprosy, operational classification (paucibacillary or multi-bacillary), Ridley-Jopling classification (indeterminate, tuberculoid, borderline tuberculoid, midborderline, borderline lepromatous, and lepromatous), and simplified neurological examination according to Brazilian Ministry of Health guidelines
Conventional diagnostic tests	Slit skin smear results, bacillary index, and histopathological findings from skin or nerve biopsy (when performed)
Index test—PCR^b^ from perineural aspirate	PCR detection of Mycobacterium leprae targets: RLEP, sodA, and 16S rRNA^c^
Complementary diagnostic test—ultrasound examination	Nerves evaluated: median nerve (carpal tunnel and pronator quadratus), ulnar nerve (ulnar tunnel, immediately before the ulnar tunnel, Guyon canal, and immediately before the Guyon canal), common fibular nerve (fibular head), and tibial nerve (tarsal tunnel and 4 cm above the tarsal tunnel); CSA^d^ measurements; asymmetry indexes (change in CSA^e^ and CSA ratio); focality indexes (change in TPT^f^ and TPT ratio); intraneural or epineural Doppler signal (hypervascularity); nerve echogenicity (normal or abnormal); loss of fascicular pattern; and focal nerve thickening
Reference standard (composite clinical diagnosis)	Presence of ≥1 cardinal sign of leprosy: (1) definite sensory loss in a hypopigmented or reddish skin lesion, (2) thickened or enlarged peripheral nerve with sensory loss and/or muscle weakness, and (3) acid-fast bacilli in slit skin smear

^a^WHO: World Health Organization.

^b^PCR: polymerase chain reaction. PCR targets: RLEP, sodA, and 16S ribosomal RNA of *M leprae*.

^c^rRNA: ribosomal RNA.

^d^CSA: cross-sectional area of the nerve.

^e^Absolute difference between contralateral nerves.

^f^TPT: difference between the thickest and thinnest points along the nerve.

**Figure 1 figure1:**
[figure not shown]
Schematic representation of the study workflow, including patient recruitment, ultrasound evaluation, perineural aspiration, and molecular testing. CSA: cross-sectional area; MB: multi-bacillary; PB: paucibacillary; PCR: polymerase chain reaction; rRNA: ribosomal RNA; WHO: World Health Organization.

### Ultrasound Examination

The equipment used will be the Versana Active model (GE HealthCare) with a high-frequency multifrequency golf club transducer (18 MHz). The nerves evaluated will be (1) the median nerves at the carpal tunnel and at the level of the pronator quadratus, (2) the ulnar nerves in the ulnar tunnel and immediately before the ulnar tunnel and at the Guyon canal and immediately before the Guyon canal, (3) the common fibular nerve in the head of the fibula, and (4) the tibial nerve at the level of the tarsal tunnel and 4 cm above the tarsal tunnel. The measurements to be performed will comprise the areas obtained in the cross-section, drawing a continuous line around the nerve margin in the region of greatest thickness. All nerves in both sides of the body will be studied in the axial and transverse planes, and power Doppler will be used to detect signs of inflammation in each studied area.

The calculation of neural asymmetry or its exclusion will be determined using the following data: absolute cross-sectional area (CSA) value, asymmetry indexes (change in CSA and CSA ratio), and focality indexes (change in the difference between the thickest and thinnest points along the nerve [TPT] and TPT ratio). These are defined as follows [21]: (1) change in CSA is the absolute difference in CSA between corresponding right and left nerves at the same anatomical site, (2) CSA ratio is the ratio between the CSAs of the same nerve on opposite sides of the body—right and left, (3) change in TPT is the absolute difference between the CSA at the point of interest and a nearby reference segment of the same nerve, and (4) TPT ratio is a ratio comparing the CSA at the enlarged site with a nearby reference site. Change in TPT and TPT ratio will only be measured in the cubital and carpal tunnels.

The areas will be used to calculate asymmetry, and the value of the bilateral absolute differences of each nerve in relation to the contralateral side will be determined. Normal values for comparison were obtained from the literature.

Color Doppler will be performed with a pulse repetition frequency of 0.7 to 1.0 kHz, and intraneural or epineural color detection will be considered indicative of hypervascularity.

Nerve echogenicity will be classified as normal or abnormal. A hypoechoic pattern, one with hypoechoic areas, or even one that presents focal thickening with loss of fascicular pattern will be considered abnormal.

The examinations will be performed by 2 radiologists with prior training in sonographic neural imaging blinded to the clinical examination of the patients to ensure the impartiality of the study. A third radiologist will be responsible for calculating CSA, change in CSA, CSA ratio, change in TPT, and TPT ratio based on deidentified images collected during ultrasound examination.

### Fine Needle Aspiration

Perineural aspiration will be performed in the ultrasound room of the dermatology outpatient clinic of the UHB. Asepsis and antisepsis of the skin over the collection site will be followed via ultrasound-guided insertion of a 26G needle that is connected to a 1-mL syringe (insulin). The syringe will be prefilled with 0.6 mL of sterile saline solution, with the needle being inserted in a parallel direction to the nerve with constant negative pressure. This procedure will be repeated 3 times. The aspirate will be placed in two 1.5-mL microtubes (Axygen), with 0.3 mL of Invitrogen RNAlater solution (Thermo Fisher Scientific) added to the tube designated for RNA extraction. The samples will be stored at −80 °C until nucleic acid extraction.

